### Control

Participants receive nonpersonalized HIV prevention information, including free HIV testing and condom use, following the guidelines provided by the Chinese Center for Disease Control and Prevention and the operational standards of the community organizations, with twice-weekly information push notifications.

### Outcomes

The primary outcome indicator of this study is the rate of PrEP initiation, based on formal PrEP prescriptions issued by doctors. The secondary outcome indicators include medication adherence rates after initiating PrEP (based on self-reported adherence and the medication calendar in the mini-program), intention to pay for PrEP (for 3 types of PrEP), PrEP stigma, changes in condom use, and changes in number of sexual partners before and after PrEP use.

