### Study Population and Participant Recruitment

The study population is sourced from 3 MSM-friendly CBOs located in different regions. The inclusion criteria for community organizations are: (1) the organization must meet the sample size requirements for the project; (2) there must be a willingness to collaborate, making PrEP promotion a work priority; and (3) the organization should have a good partnership with local hospitals or centers for disease control and prevention to coordinate with disease control specialists and HIV specialists. Community collaborators participate in project training, assist with participant recruitment, support baseline and follow-up surveys, and help with quality control. Participants included in this study must meet the following criteria: (1) aged 18 years or older; (2) assigned male sex at birth and have had sexual intercourse with men in the past 6 months; (3) HIV negative at the start of the study; (4) no prior PrEP using experience; (5) willing to participate in the PrEP intervention and voluntarily consent to complete data collection and follow-up according to the assigned protocol; (6) classified as high risk for HIV infection in the past 6 months as suggested by the “Expert Consensus on HIV Pre-Exposure Prophylaxis in China (2023)” [7]. Participants are excluded if they meet any of the following criteria: (1) HIV positive, or unaware of their HIV status and refuse to undergo HIV testing; (2) have a health condition that makes PrEP unsuitable; and (3) have cognitive impairments or other severe illnesses that may affect the informed consent process.

The sample size calculation was based on the formula for an individually randomized controlled trial, assuming a 2-sided significance level (*α*) of .05 and type II error rate (*β*) of .10 (90% power). Based on extant literature and a 2021 multicenter PrEP survey in China indicating a median current PrEP usage rate (*p₁*) of 5% among MSM, the target post-intervention usage rate (*p₂*) was set at 20%. This yielded a minimum requirement of 100 participants per group. Accounting for an anticipated 15% attrition rate, the sample size was increased to 126 participants per group, resulting in a total target enrollment of 378 participants (126 per group) across 3 CBOs.

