### Ethical Considerations

The study protocol was approved by the Ethics Commission of Peking University Health Science Center (IRB00001052-24167) on December 22, 2024. Prior to study initiation, all participants are fully informed about the study objectives, procedures, potential risks, and their rights, and provide written informed consent. Participants receive a compensation of US $2.8 (approximately CNY 20) for completing each questionnaire at baseline and follow-up assessments. The study does not provide free PrEP medication; participants are required to purchase medications at market prices. To protect participant privacy and confidentiality, several measures have been implemented: data collection uses a customized WeChat mini-program featuring local data storage and optional fingerprint authentication for enhanced privacy; all questionnaires are administered anonymously and linked only via a unique study ID; and sexually transmitted infections test results (HIV, syphilis, hepatitis B, and hepatitis C) are recorded solely as binary (positive or negative) outcomes without any personally identifiable information.

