#### Evaluation of Intervention Effectiveness

This study will use mixed-effects models to evaluate the effectiveness of primary and secondary outcome indicators. Different evaluation models will be selected based on the type of outcome indicators. Individual participants will be the unit of analysis. For the evaluation of categorical variable effects, a generalized mixed linear model will be used, reporting the adjusted odds ratio. For continuous variable effects, a mixed linear model will be used, reporting the adjusted mean differences between groups. The effectiveness evaluation will adhere to the intention-to-treat principle, including all randomized participants in the analysis. Stratified analysis will be conducted based on participants’ age, education level, income level, sample source, and city characteristics to explore evidence of effects related to these various characteristics. Statistical analyses will be performed using R (R Foundation for Statistical Computing) and SPSS software (IBM Corp), with a *P* value<.05 considered statistically significant. The study assumes that missing values are randomly distributed, and missing data will be handled using maximum likelihood estimation. Sensitivity analyses will be conducted after imputing missing values using multiple imputation methods.

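### Adherence is defined only after PrEP initiation, so the all-randomized analysis rule cannot be applied to it and a comparison among initiators is not a randomized one

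*Protocol article*

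**What the plan says.** All references are to the protocol article.

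- **Aim.** The Abstract's Objective and the last paragraph of the Introduction name adherence, beside initiation, as something the interventions are meant to improve.
- **Definition.** Outcomes lists as a secondary outcome "medication adherence rates after initiating PrEP (based on self-reported adherence and the medication calendar in the mini-program").
- **Entry.** Study Population and Participant Recruitment admits only men who have never used PrEP.
- **Analysis set.** Evaluation of Intervention Effectiveness assigns mixed-effects models to the primary and secondary outcomes and states: "The effectiveness evaluation will adhere to the intention-to-treat principle, including all randomized participants in the analysis". Missing values are handled by maximum likelihood, with multiple imputation as sensitivity analysis. Participants who never start PrEP are not mentioned.
- **Initiation.** It means a physician's prescription (Outcomes; Conditional Economic Incentives). Ethical Considerations adds: "The study does not provide free PrEP medication; participants are required to purchase medications at market prices".
- **Sexual behavior.** Outcomes lists "changes in condom use, and changes in number of sexual partners before and after PrEP use". Measurements and Follow-Ups collects partner number and condom use at baseline, and again at follow-up as a change from baseline, without limiting this to PrEP starters.

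**The concern.** Starting PrEP is a post-randomization event that the interventions are built to influence. Adherence as worded exists only for those who start. Two problems follow.

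First, the blanket all-randomized rule has nothing to act on for most participants. Taken literally together with the missing-data plan, it would treat the adherence of men who never started as missing and impute it, although no such value exists.

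Second, the natural way out is to compare initiators across arms. That conditions on the primary outcome. Control starters would be men who sought a prescription with only general prevention information. Active-arm starters would include men moved by motivational interviews or by a payment tied to their group's prescription rate. A difference in adherence between those sets could reflect who started rather than what the intervention did to pill-taking.

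At stake is the conclusion on adherence, one of the two behaviors that the trial says it will improve.

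**Working it through.** **1. The plan's own figure.** Inputs from Study Population and Participant Recruitment: "assuming a 2-sided significance level (*α*) of .05 and type II error rate (*β*) of .10 (90% power"), "a median current PrEP usage rate (*p₁*) of 5% among MSM", and "the target post-intervention usage rate (*p₂*) was set at 20" percent. With the pooled-variance formula and mean rate 0.125:

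n = [1.960·√(2·0.125·0.875) + 1.282·√(0.05·0.95 + 0.20·0.80)]² / 0.15² = (0.917 + 0.584)² / 0.0225 ≈ 100.1, or 101 rounded up.

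The stated minimum of 100 per group is reproduced. The 5% and 20% are therefore the rates the design rests on, and they are used below.

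**2. Expected initiators.** Arm sizes are from Participant Recruitment in Results.

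| Arm | Randomized | Planning rate | Expected initiators |
|---|---|---|---|
| Control | 127 | 5% | 6.35 |
| HAPA | 128 | 20% | 25.6 |
| HAPA+GCEI | 126 | 20% | 25.2 |

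The 95% binomial range for control is 2 to 12. With the planned 15% attrition, 127 × 0.85 ≈ 108 and 108 × 0.05 = 5.4. If control initiation were 10%, an assumption, 127 × 0.10 = 12.7.

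**3. Precision among initiators.** Assume 40% adherence in both arms, which lies within the 29.9% to 41.1% quoted in the Introduction.

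- 6 vs 25: 1.96·√(0.24/6 + 0.24/25) = 1.96·√0.0496 = 0.44.
- 13 vs 25: 1.96·√(0.24/13 + 0.24/25) = 1.96·√0.0281 = 0.33.

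**4. Power among initiators, 6 vs 25, two-sided 0.05.**

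- 29.9% vs 41.1%: 6% by normal approximation, 3% by Fisher's exact test.
- 35% vs 65% (assumed): 26% and 17%.
- From an assumed 35% in control, the other arm would need about 89% for 80% power (normal approximation).

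**5. An all-randomized definition.** If non-initiators count as not adherent, the denominators are 127, 128 and 126. At the planning rates and 40% adherence among starters in every arm, the expected proportions are 0.05 × 0.40 = 2% in control and 0.20 × 0.40 = 8% in an active arm. The difference is 6 points. Its rough half-width for 127 vs 126 is 1.96·√(0.02·0.98/127 + 0.08·0.92/126) = 0.053. The approximation is crude, because control would have only 127 × 0.02 ≈ 2.5 events. In this example the whole difference comes from starting, since adherence among starters was set equal.

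**6. Sexual behavior, sections side by side.** In Outcomes, the closing phrase that refers to PrEP use attaches to partner number and only ambiguously to condom use. Measurements and Follow-Ups measures both against baseline in participants generally. An all-randomized comparison is possible with data already collected, so the defect is a mismatch in wording.

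**The case against.** The strongest reply is that the article never says how adherence will be compared. It gives a general intention-to-treat rule, says that models will vary by outcome type, and schedules no P value for initiators alone. Analysis sets for individual secondary outcomes are often left to a full protocol or analysis plan, which is not at hand. This stands in part: nobody can say that an initiator-only test is planned. But the article itself fixes both the definition and the analysis set, and for this outcome they conflict. That is a conflict in what is stated, not a missing detail.

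The figure of 6 is an expectation. It applies a survey rate of current use to three-month initiation in recruited, high-risk men willing to join a PrEP study. The true count could well be higher. The loss of randomization does not depend on it.

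Three stronger readings are tempting and not supported.

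- A reader might infer that condom use and partner number are also limited to initiators. Measurements and Follow-Ups shows that they are not.
- A reader might infer that selection will make the interventions look worse on adherence. This depends on an assumed link between motivation, starting and adhering. In one illustrative model with no true effect, the apparent deficit is 0, 1.8, 4.1 (58.2% vs 54.1%) or 6.5 points (65.3% vs 58.8%) as the assumed link rises from none to strong. Its initiators also adhere more often than the Introduction's range suggests. The documents fix neither direction nor size.
- A reader might infer that analyzing everyone would hide a prescription obtained but never filled. The reverse is true: under an initiated-and-adherent outcome that man counts as not adherent.

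**Conclusion.** The point holds for adherence. As defined, it cannot be analyzed in all randomized participants, and a comparison among initiators conditions on a post-randomization event that the interventions aim to change. At the plan's 5% and 20% that comparison would have about 6 against about 25 participants per pair of arms, with a half-width of about 44 points at an assumed 40% adherence. At an assumed 10% control initiation it would still be about 33 points. Such a comparison could neither establish nor exclude a realistic effect.

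For condom use and partner number, what remains is an inconsistency between two sections.

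This should be fixed, but it does not threaten the trial. Adherence is secondary, and the prescription-based primary outcome is defined for everyone randomized.

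**What to change.** 1. For the between-arm comparison, define adherence in all randomized participants as PrEP initiated and adherent at each follow-up. Count non-initiators as not adherent and do not impute adherence for them. The article names the data sources but no cut-off, so the investigators should fix a threshold before unblinding.
2. Report adherence among initiators by arm as descriptive only, with counts and without tests.
3. Reword the Outcomes entry for condom use and partner number as change from baseline to each follow-up in all randomized participants, by arm, to match Measurements and Follow-Ups.

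The cost is revised wording and recoding of data already being collected. It can be settled before the database lock planned for December 2026. The drawback is that the new outcome mixes starting with adhering and will partly repeat the primary result, so the initiator-only rates should stand beside it.

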### Measurements and Follow-Ups

For the questionnaire survey, participants are informed about the study’s objectives, content, and procedures, and they sign an electronic informed consent form. The following baseline assessment questionnaire is conducted via a mini-program:

Demographic characteristics: Includes age, ethnicity, education level, marital status, employment status, income level, and sexual orientationSexual behavior characteristics: Includes age at first sexual intercourse, types and number of sexual partners, sexual roles, condom use, HIV testing, and whether they have paid or have been paid for sexPrEP usage intentions and behaviors: Includes a PrEP knowledge assessment questionnaire, awareness rates and sources of information about PrEP, willingness to use and pay for PrEP, past PrEP usage, types of PrEP, frequency of use, and willingness to use different types of PrEPHAPA-based PrEP cognition scale: Includes self-efficacy for initiating, maintaining, and resuming PrEP use, positive outcome expectations for PrEP, negative outcome expectations for PrEP, perceived HIV risk, willingness to use PrEP, and action plans for initiating and maintaining PrEP use. This scale has been developed and validated among the MSM population, comprising 9 dimensions and 44 items, using a 5-point Likert scale from 1 (“strongly disagree”) to 5 (“strongly agree”), with a total Cronbach α of 0.882 [35]PrEP Stigma Scale: Uses a 10-item HIV PrEP Stigma Scale, which has been validated in multiple countries, eg, “using PrEP will lead to negative evaluations by others.” The scale uses a 5-point Likert score from 1 (“strongly disagree”) to 5 (“strongly agree”), with higher scores indicating greater PrEP stigma, and a Cronbach α of 0.880 [36].

Follow-ups are conducted at the end of the intervention and 3 months later. The follow-up questionnaire builds upon the baseline assessment, focusing on the following key areas:

Intervention process and satisfaction evaluation: This evaluates participants’ experience and satisfaction with the mobile health intervention platform (the WeChat mini-program), including usage frequency, overall satisfaction, willingness to recommend it, and specific feedback on its ease of use, interface design, information resources, medication reminders, recording functions, and data privacy protection.Risk compensation behavior assessment: It investigates changes in participants’ sexual behavior patterns during the intervention to assess the possibility of risk compensation, including changes in the frequency of same-sex intercourse, number of male sexual partners, and condom use frequency compared to baseline.PrEP uptake status: Based on the current PrEP status at follow-up, it further explores specific reasons for noninitiation or discontinuation, sources of medication acquisition, methods of recording medication use, episodes of treatment interruption, occurrence of adverse drug reactions, partner awareness, psychological experiences related to PrEP use, and willingness to recommend it.Dynamic measurement of PrEP-related cognition: It reapplies key items from the validated HAPA-based PrEP cognition scale to assess changes in postintervention cognition, including self-efficacy for PrEP initiation and maintenance, positive and negative outcome expectations, perceived HIV risk, and action planning.Reassessment of PrEP decision and payment willingness: It re-evaluates participants’ perception of pricing and willingness to use different PrEP regimens at market prices, as well as their views on potential models for cost-sharing.Follow-up on PrEP perceived stigma and MSM group cohesion: It uses a brief mental health scale to assess emotional states over the past week, remeasures PrEP perceived stigma levels, and evaluates changes in perceived cohesion within the MSM community.

The sexually transmitted infections testing data (HIV, syphilis, hepatitis B, and hepatitis C) from participants at baseline and during 2 follow-up visits are collected. All tests are performed using standardized diagnostic kits (Wondfo Biotech) according to the manufacturer’s protocols. Serological results are recorded as binary outcomes (positive or negative). For participants who initiated PrEP during the study, adverse drug reaction evaluations are integrated throughout the PrEP medical service process. A formal safety stopping rule is prespecified. The trial will be halted immediately if the independent Data and Safety Monitoring Board identifies clear, serious, and related adverse events attributable to the study procedures that pose unacceptable risks to participants, or if new, definitive external evidence emerges that renders the trial unethical or obsolete.

### Preliminary Testing and Modifications

Preliminary testing with key stakeholders enabled critical refinements to study instruments and procedures, including substantial enhancements to the WeChat mini-program’s navigation flow to facilitate access to PrEP information and intervention components, along with added privacy protection features such as local data storage and optional fingerprint authentication, while message delivery timing was optimized based on observed user activity patterns. Questionnaire modifications involved clarifying wording in the PrEP Stigma Scale to better differentiate between perceived and internalized stigma, and supplementing HAPA-based scales with concrete examples to improve comprehension of abstract constructs like self-efficacy.

The motivational interview protocol is finalized after cultural appropriateness testing, resulting in standardized prompts for exploring financial and structural barriers specific to Chinese MSM populations, as well as incorporating guidance for discussing newly approved LAI-PrEP options, collectively strengthening the intervention’s relevance and implementation fidelity for the target population.

### Ethical Considerations

The study protocol was approved by the Ethics Commission of Peking University Health Science Center (IRB00001052-24167) on December 22, 2024. Prior to study initiation, all participants are fully informed about the study objectives, procedures, potential risks, and their rights, and provide written informed consent. Participants receive a compensation of US $2.8 (approximately CNY 20) for completing each questionnaire at baseline and follow-up assessments. The study does not provide free PrEP medication; participants are required to purchase medications at market prices. To protect participant privacy and confidentiality, several measures have been implemented: data collection uses a customized WeChat mini-program featuring local data storage and optional fingerprint authentication for enhanced privacy; all questionnaires are administered anonymously and linked only via a unique study ID; and sexually transmitted infections test results (HIV, syphilis, hepatitis B, and hepatitis C) are recorded solely as binary (positive or negative) outcomes without any personally identifiable information.

### Statistical Analysis

#### Descriptive Analysis of Baseline Data and Intergroup Comparisons

For numeric variables such as PrEP usage intentions and HAPA component scores, the mean and SD (or median and IQR) will be reported based on the data distribution. Mann-Whitney tests or *t* tests will be used to compare the baseline data balance between the intervention and control groups according to the data distribution type. Categorical variables such as PrEP initiation and adherence will be described using rates, and chi-square tests or Mann-Whitney tests will be used to compare the baseline data balance between the intervention and control groups.

#### Evaluation of Intervention Effectiveness

This study will use mixed-effects models to evaluate the effectiveness of primary and secondary outcome indicators. Different evaluation models will be selected based on the type of outcome indicators. Individual participants will be the unit of analysis. For the evaluation of categorical variable effects, a generalized mixed linear model will be used, reporting the adjusted odds ratio. For continuous variable effects, a mixed linear model will be used, reporting the adjusted mean differences between groups. The effectiveness evaluation will adhere to the intention-to-treat principle, including all randomized participants in the analysis. Stratified analysis will be conducted based on participants’ age, education level, income level, sample source, and city characteristics to explore evidence of effects related to these various characteristics. Statistical analyses will be performed using R (R Foundation for Statistical Computing) and SPSS software (IBM Corp), with a *P* value<.05 considered statistically significant. The study assumes that missing values are randomly distributed, and missing data will be handled using maximum likelihood estimation. Sensitivity analyses will be conducted after imputing missing values using multiple imputation methods.

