#### Conditional Economic Incentives

Participants in the combined intervention arm also receive additional peer GCEIs on top of the HAPA intervention. Incentive information is communicated immediately at the start of the intervention. The incentive amounts are determined at the end of the 3-month intervention by the researchers based on the overall completion status of each participant and their peer group according to predetermined conditions.

Participants are formed into peer groups of approximately 6 individuals. These groups participate in structured in-person sessions. Activities are designed to include: introductions and icebreakers, PrEP knowledge quizzes, partner dialogues, “Voicing My Barriers” roundtable discussions, and PrEP scenario role-playing. The objectives are to foster trust, enable deeper peer connection, enhance group belonging, strengthen HIV prevention awareness, identify and overcome barriers to PrEP use, and ultimately increase PrEP initiation rates. Six participants form a peer group, and the economic incentive amount is based on the average completion level of the group. Group-level economic incentives are stepwise reduced based on the group’s average PrEP initiation rate. Participants qualify for US $22 if their group achieves an 80%‐100% rate, US $11 for a 50%‐79% rate, and US $0 for rates below 50%. PrEP initiation is operationally defined as the documented provision of a physician-issued prescription.

The WeChat mini-program automatically records intervention process evaluation indicators, including: (1) whether each participant has read the information messages; (2) the reading time for each message; and (3) each participant’s judgment of whether the information was helpful.

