### Participant Recruitment

Participant recruitment and screening were conducted from October to December 2025. During this period, 743 eligible MSM from the 3 CBOs were initially identified and assessed. Of these, 362 individuals were excluded for the following reasons: failure to meet predefined inclusion criteria (n=306), declining to participate (n=52), or other logistical reasons (n=4). Consequently, 381 participants provided written informed consent and were formally enrolled in the study. These 381 participants were randomly allocated into 1 of 3 study arms using a computer-generated sequence: HAPA-based cognitive behavioral intervention group (n=128), HAPA plus GCEI intervention group (n=126), and control group (n=127).

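### Peer groups of six make outcomes in the HAPA+GCEI arm correlated by design, but the sample size makes no allowance for this and the analysis section names no peer-group effect

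*Protocol article*

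**What the plan says.** Participants are randomized individually to three arms. Under Conditional Economic Incentives, only the combined arm is then formed into peer groups, which meet in person: "Six participants form a peer group, and the economic incentive amount is based on the average completion level of the group". The payment is stepped according to the group's initiation rate, with initiation defined by a physician's prescription. The Outcomes section makes prescription-based initiation the primary outcome, so the payment rule and the primary endpoint use the same event.

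Under Study Population and Participant Recruitment, "The sample size calculation was based on the formula for an individually randomized controlled trial", with two-sided alpha .05, 90% power, and rates of 5% and 20%. "This yielded a minimum requirement of 100 participants per group", and then: "Accounting for an anticipated 15% attrition rate, the sample size was increased to 126 participants per group". No ICC or design effect appears.

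Under Evaluation of Intervention Effectiveness, mixed-effects models are planned for the primary and secondary outcomes, and "Individual participants will be the unit of analysis". No random effect is named. City and sample source are mentioned for stratified analysis; peer group is not mentioned.

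The Results section reports the allocation as HAPA n=128, "HAPA plus GCEI intervention group (n=126), and control group (n=127").

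**The concern.** Grouping in one arm only makes this a partially nested design. The Introduction presents peer influence and shared accountability as the way the incentive works, and the payment rewards members of a group for initiating together. Positive correlation of initiation within a group is therefore the intended mechanism, and an ICC of exactly zero would be hard to defend.

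Two things follow. First, 126 participants in 21 groups carry less information than 126 independent participants, so a sample size based on independence overstates power for the HAPA+GCEI contrasts. Second, a model without a peer-group term gives standard errors that are too small for HAPA+GCEI versus control and for HAPA+GCEI versus HAPA. The trial hypothesizes that this arm will do best, so the inflated error rate would fall on the main claim.

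**Working it through.** **Inputs from the protocol.** Two-sided alpha .05; power 90%; p1 = 0.05; p2 = 0.20; 100 per group; 15% attrition; 126 per group; peer groups of about 6.

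**Assumed.** The ICC. The document gives no value, so a range from 0 to 0.20 is shown.

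**1. The plan's own figure.** With pooled variance under the null and mean rate 0.125:

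n = [1.96·√(2·0.125·0.875) + 1.2816·√(0.05·0.95 + 0.20·0.80)]² / 0.15² = 100.06

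This is 100, or 101 rounded up. Power at exactly 100 per group is 90.0%. The stated minimum therefore reproduces with independent participants and leaves no room for a design effect.

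**2. Numbers retained.** 126 × 0.85 = 107 per arm. The attrition step alone would give 100/0.85 = 118, so 126 carries some slack that the protocol does not explain. Over 21 groups, 107/21 = 5.1 members are retained per group.

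**3. Power for HAPA+GCEI versus control with clustering in one arm.** The variance of the HAPA+GCEI arm is multiplied by DE = 1 + (m − 1)·ICC, where m is the group size:

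- SE0 = √[0.125·0.875·(1 + DE)/n]
- SE1 = √[(0.05·0.95 + 0.20·0.80·DE)/n]
- Power = Φ[(0.15 − 1.96·SE0)/SE1]

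Example: n = 100, m = 6, ICC = 0.05 gives DE = 1.25, SE0 = 0.0496, SE1 = 0.0497, and Φ(1.061) = 85.6%.

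| ICC | n=100, m=6 | n=107, m=6 | n=107, m=5.1 | n=126, m=6 |
|---|---|---|---|---|
| 0 | 90.0% | 91.8% | 91.8% | 95.4% |
| 0.01 | 89.1% | 91.0% | 91.2% | 94.8% |
| 0.02 | 88.2% | 90.2% | 90.5% | 94.2% |
| 0.05 | 85.6% | 87.8% | 88.5% | 92.4% |
| 0.10 | 81.2% | 83.7% | 85.2% | 89.0% |
| 0.20 | 73.3% | 76.0% | 78.7% | 82.3% |

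The two columns for 107 differ in whether groups stay at six or shrink with attrition. Power of 90% is kept up to an ICC of about 0.02 (m = 6) or just under 0.03 (m = 5.1). With no loss at all, it is kept up to about 0.085.

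**4. Type I error if peer group is left out.** With equal arms, the true variance of the difference is (1 + DE)/2 times the variance that the test assumes:

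Type I error = 2·[1 − Φ(1.96/√((1 + DE)/2))], with m = 6

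| ICC | DE | Formula | Simulation |
|---|---|---|---|
| 0.02 | 1.10 | 5.6% | 5.4% |
| 0.05 | 1.25 | 6.5% | 6.2–6.3% |
| 0.10 | 1.50 | 8.0% | 7.6% |
| 0.20 | 2.00 | 11.0% | 10.3–11.2% |

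The simulation drew beta-binomial outcomes for 21 groups of 6 against 126 independent participants, with a common true rate of 5% or 20%. The same inflation applies to HAPA+GCEI versus HAPA, because HAPA participants are not grouped. HAPA versus control involves no peer groups.

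**The case against.** A reader might infer that the plan analyses everyone as independent, so that the P values for this arm are too small as the plan stands. The text does not support that. Mixed models exist to handle non-independence, and a generalized mixed model with one row per person and a random intercept for peer group still has the individual as its unit. The article leaves the random-effects structure open, and an unseen analysis plan may specify it. This objection stands: the type I error figures apply only if peer group is omitted. They still matter, because the section as written would be met equally by a model with random effects for repeated visits or for city, and neither captures peer group.

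A reader might also infer that the 90% power fails outright. That too goes further than the documents allow. It is certain only at the stated minimum of 100. The slack in 126 absorbs a small ICC, and at an ICC of 0.05 with 107 retained the shortfall is about 2 points.

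Finally, randomization is complete, so restating power changes nothing about how the trial is run. That is so, but it affects how a null or borderline HAPA+GCEI result should be read. The sample size is fixed in this document, so a later analysis plan cannot add the missing allowance.

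**Conclusion.** The point holds in two parts of different strength.

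- **Sample size: established from the text.** The calculation makes no allowance for correlation that the design sets out to create. For HAPA+GCEI versus control, power at 100 per group is below 90% for any positive ICC (85.6% at 0.05, 81.2% at 0.10). With 107 retained per arm, it is about 88%, 84–85% and 76–79% at ICCs of 0.05, 0.10 and 0.20.
- **Analysis: conditional.** If peer group is left out of the model, type I error for the two HAPA+GCEI contrasts is about 5.6% to 11.0% over ICCs of 0.02 to 0.20. The document does not show that it will be left out; it does not commit to including it.

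All of these sizes rest on an assumed ICC, on groups of about six and on normal approximations. The power figures use the protocol's 5% and 20%. They do not describe HAPA+GCEI versus HAPA, for which the protocol gives no target difference.

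**What to change.** Keep the individual as the unit of analysis. Add to Evaluation of Intervention Effectiveness that the model for the two HAPA+GCEI contrasts includes a random peer-group effect in the HAPA+GCEI arm only, with every other participant treated as a singleton. Group-robust variance with a small-sample correction for about 21 groups is an acceptable alternative. In the sample size paragraph, replace the flat 90% for HAPA+GCEI versus control with power over a range of ICCs, and state the target difference and power for HAPA+GCEI versus HAPA if that contrast is to be claimed. Settle this before database lock, which is planned for December 2026.

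No new participants are needed, and the group membership must already be recorded to work out the payments. There are two costs. Intervals for the HAPA+GCEI contrasts become somewhat wider. Also, a group code that exists in one arm only would reveal that arm to analysts whom the protocol describes as blinded. To limit this, give every other participant a unique dummy group code and add the variable only when the final model is run.
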